#### Process evaluation and intervention acceptability

Interviews will be recorded, transcribed verbatim and initially analysed inductively using Thematic Analysis (74), which will be facilitated using NVivo software (QRS International Pty Ltd, Victoria, Australia). This will enable identification of themes relative to APEASE, such as intervention acceptability (e.g. barriers and facilitators to engagement), appropriateness of data collection procedures and feasibility of delivering the health coaching support. Anonymous quotations (using pseudonyms) will be used from the interviews to illustrate the themes identified. Rating scales concerning the intervention will be analysed using descriptive statistics (means, SD, frequencies) and the open-ended responses will be used to identify relevant themes that may explain the quantitative responses provided.

#### Preliminary effects of the intervention

Descriptive statistics will be calculated to summarise the primary (device measured daily sitting time) and secondary outcomes (device measured prolonged sitting, breaks in sitting time, standing and stepping; body composition; cardiometabolic risk markers; psychological, sleep, musculoskeletal and wellbeing outcomes; physical function) and explore trends in the data. Continuous data will be summarised in terms of mean and standard deviation. Categorical data will be summarised in terms of frequency, counts and percentages. All baseline variables will be tabulated (no. (%), mean (SD)) by the treatment allocation and overall. Statistical analyses will be performed using SPSS v22 (IBM, Armonk, NY, USA).

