## RESEARCH OBJECTIVES

The main objectives of this feasibility study are to:

1. Establish and refine a recruitment strategy for people with Type 2 diabetes.
2. Determine participant attrition in the trial.
3. Determine completion rates for outcome measures (and whether these are sufficiently high to provide accurate data in a full trial).
4. Assess the acceptability of randomisation to the intervention and usual care.
5. Assess the acceptability of the intervention and data collection to participants.
6. Assess intervention fidelity and adherence.
7. Explore the feasibility of collecting data (as below) to inform the design of the health economics component in a full RCT.

The secondary objectives are to derive preliminary estimates of the effect of the intervention on participants’:

1. Device measured daily sitting time, prolonged sitting time, breaks from sitting and light and moderate-to-vigorous physical activity.
2. Cardiometabolic risk markers (BMI, waist circumference, body fat%, fasting glucose, glycated haemoglobin, lipids, blood pressure)
3. Fatigue, self-efficacy for reducing sitting time, psychological wellbeing, mood, physical functioning, musculoskeletal symptoms and quality of life.

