### Sample size

Sample sizes between 24 and 50 have been recommended for feasibility studies (46, 47). A sample size of 70 will be used in this study (n=35 in each the intervention and control groups) to allow for the different combination of intervention tools that the participants are able to select from and to allow for drop out.

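### The secondary objective is to estimate intervention effects, but the stated outcome analysis gives descriptive summaries only, with no between-arm difference or confidence interval

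*Protocol*

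**What the plan says.** Research Objectives (Protocol) lists seven main objectives, all about feasibility, and then states: "The secondary objectives are to derive preliminary estimates of the effect of the intervention on" three groups of participant outcomes. These are activPAL sitting and activity measures, cardiometabolic markers, and patient-reported and functional measures.

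The only analysis text for these outcomes is Data analysis, subsection Preliminary effects of the intervention. It opens with "Descriptive statistics will be calculated to summarise the primary (device measured daily sitting time) and secondary outcomes", and adds the aim of looking for trends. On how numerical outcomes are to be reported, it has one sentence: "Continuous data will be summarised in terms of mean and standard deviation". Outcomes recorded in classes get only counts and shares. A by-arm layout is then promised in a single place: "All baseline variables will be tabulated (no. (%), mean (SD)) by the treatment allocation and overall".

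That sentence is the only one in the subsection that mentions allocation, and it concerns baseline variables. Under Data collection, the measures are scheduled at baseline, 12 and 24 weeks. COVID-19 contingencies would remove some of them.

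**The concern.** In a 1:1 randomised trial against usual care, an estimate of the intervention effect is a contrast between arms, and it is usable only with a statement of its uncertainty. The analysis section carries the word effects in its heading, but none of its listed outputs is an effect. It does not even say that the 12- and 24-week results will be split by arm, so a table of change over time in the whole sample, or within each group, would comply.

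At stake is how the effect data will be read. Readers would have to compare follow-up means by eye over many outcomes and two time points, with no interval to show how little a trial of 70 can say about each. Such judgements are foreseen: the investigator committee reviews efficacy data, and the process evaluation asks whether the intervention works.

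**Working it through.** **1. Objective against analysis.** The question is whether each component of an effect estimate appears in the protocol.

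| Component | Stated? |
| --- | --- |
| Follow-up outcomes summarised by arm | No; by-arm tabulation is stated for baseline variables only |
| Between-arm difference | No |
| Confidence interval or standard error of a difference | No |
| Mean and SD; counts and percentages | Yes |

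No other section supplies the missing items. The remaining Data analysis subsections cover recruitment, retention and completion rates, and the interviews and rating scales.

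**2. Is there a planned precision to reproduce?** No. Sample size takes 70 (35 per arm) from published feasibility recommendations of 24 to 50, plus an unquantified allowance for tool combinations and dropout. It gives no SD, effect size, power or dropout rate.

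**3. How wide the missing interval would be.** This is an illustration for daily sitting time. The inputs below are assumptions, except for the 35 per arm.

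- Analysed per arm: n = 28, from 35 × (1 − 0.20), with 20% loss assumed.
- SD of sitting time: 90 to 120 min/day.
- Baseline to follow-up correlation r: 0 (unadjusted), 0.5 or 0.7.

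Half-width of the 95% CI = t(0.975, df) × SD × √(2/n) × √(1 − r²), with df = 2n − 2 unadjusted and 2n − 3 adjusted.

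For n = 28, √(2/28) = 0.267 and t is about 2.005 (df 54) or 2.006 (df 53).

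| r | Multiplier of SD | SD 90 | SD 120 |
| --- | --- | --- | --- |
| 0 | 2.005 × 0.267 = 0.536 | 48 | 64 |
| 0.5 | 2.006 × 0.267 × 0.866 = 0.464 | 42 | 56 |
| 0.7 | 2.006 × 0.267 × 0.714 = 0.383 | 34 | 46 |

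Adjustment lowers the variance by r²: 25% at r = 0.5 and 49% at r = 0.7.

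Sensitivity: with no loss (35 per arm) the unadjusted multiplier is 0.477, giving 29, 43 and 57 min/day for SDs of 60, 90 and 120.

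**4. Against the protocol's own benchmarks.** The Background cites daily reductions of 40 min and of 44 to 47 min in the two phone-app studies, and 96 min/day in the study of older adults. It also cites workplace reductions of 45 to 125 min/day, and 25 min per work shift.

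- For an observed difference of 40 min/day at SD 90, the unadjusted interval is 40 ± 48, or −8 to 88. At r = 0.7 it is 40 ± 34, or 6 to 74.
- For 96 min/day, even the widest case in the table is 96 ± 64, or 32 to 160.

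**The case against.** **It is a feasibility trial, so descriptive analysis is right.** This stands as far as hypothesis tests go, and none is asked for here. It does not answer the point, because the protocol itself makes effect estimation an objective.

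**The statistical analysis plan may supply it.** Only the protocol was available, and a separate plan may exist. Covariates and model form belong there. A reader might infer that the absence of baseline adjustment is itself a protocol error; it is not, and adjustment is only a preference. But the protocol does not defer the analysis. It states one under the matching heading, and that analysis does not produce an effect.

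**A reader could work out the difference.** This is partly right. Given by-arm means, SDs and numbers at follow-up, an unadjusted difference and interval can be calculated. However, by-arm follow-up summaries are not promised. An adjusted interval could not be recovered, because neither the change-score SD nor the correlation is a listed output.

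**Baseline values may be missing.** This stands. Under the COVID-19 contingency, body fat, height, weight, the blood markers, blood pressure and grip strength would not be taken, so adjustment can apply only where a baseline value exists.

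**The effects are secondary and preliminary.** This also stands, and it limits the severity. No progression decision in the protocol rests on them.

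**Conclusion.** The point holds. The analysis as written does not meet the secondary objective, because it contains no between-arm difference and no interval, and does not commit to by-arm summaries at follow-up. That conclusion rests on the text alone.

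The size is illustrative. With 28 per arm and an SD of 90 to 120 min/day, the half-width for sitting time is about 34 to 64 min/day, depending on adjustment. This is comparable to the smaller cited daily reductions (about 40 to 47 min/day). A reader might infer that the uncertainty is as large as any plausible effect. The figures do not support that: no case reaches 96 min/day, the smallest half-width is below 40, and SD, correlation and loss are all assumed.

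A reader might also infer that the plan fails to provide what is needed to size the full trial. Sizing that trial is not a listed objective, and SDs are planned, so this is not a failing against the protocol's own aims.

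Severity: should be fixed. The seven main objectives concern feasibility and are unaffected, and the repair can be made before analysis.

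**What to change.** In Preliminary effects of the intervention, add text to this effect:

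- Follow-up outcomes are summarised by randomised arm at 12 and 24 weeks, with the number analysed.
- For each outcome, the between-arm difference is reported with a 95% CI at each time point: a mean difference for continuous outcomes and a difference in proportions for categorical ones.
- Where a baseline value of a continuous outcome was collected, the difference preferably comes from a linear model adjusted for it. Otherwise it is unadjusted and labelled so.
- Participants are analysed in the arm to which they were randomised, and no conclusions are drawn from p-values.

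The planned descriptive tables stay. If the team does not want to estimate effects, the alternative is to reword the secondary objective as a description of outcomes. Either route costs a few lines of text; the first adds routine output from the software already named, and no extra data.

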# DISSEMINATION OF FINDINGS

Findings will be disseminated to lay, academic, practice, and policy-based audiences including:

- Summary of findings to participants via a newsletter.
- Dedicated University webpage, newsletters and social media.
- Summary report to key stakeholders in our networks e.g. Clinical commissioning group, GP practices, Diabetes UK Support Groups, Leicester Diabetes Centre.
- Publication in an international peer-reviewed journal e.g. Diabetologia.
- Presentation at conferences (e.g. International Society for Physical Activity and Health Congress).
- The National Institute for Health Research’s Collaborations for Leadership in Applied Health Research and Care, the NHS Academic Health Science Network, and the NIHR Leicester Biomedical Research Centre.

# ETHICAL AND REGULATORY COMPLIANCE

Before the start of the study, a favourable opinion will be sought from the Brunel University London Research Ethics Committee and the NHS Research Ethics Committee.

- Substantial amendments that require review by NHS REC will not be implemented until that review is in place and other mechanisms are in place to implement at site.
- All correspondence with the REC will be retained.
- It is the Chief Investigator’s responsibility to produce the annual reports as required. The Chief Investigator will notify the REC of the end of the study.
- An annual progress report (APR) will be submitted to the REC within 30 days of the anniversary date on which the favourable opinion was given, and annually until the study is declared ended.
- If the study is ended prematurely, the Chief Investigator will notify the REC, including the reasons for the premature termination.
- Within one year after the end of the study, the Chief Investigator will submit a final report with the results, including any publications/abstracts, to the REC.

The study will conform to the Declaration of Helsinki.

## GOOD CLIINICAL PRACTICE

The Chief Investigator will ensure that the study is conducted in line with the ICH Guideline for good clinical practice.

## SAFETY REPORTING

Adverse Events (AEs) are any unfavourable and unintended signs, including abnormal laboratory results, symptoms or a disease associated with treatment. If an AE occurs, this must be reported on a Case Report Form with the following information: description, date of onset and end date, severity, assessment of relatedness to study, and action taken. AEs considered related to the study as judged by the Chief Investigator will be followed until resolution or the event is considered stable. All related AEs that result in a participant’s withdrawal from the study or are present at the end of the study, should be followed up until a satisfactory resolution occurs.

Serious Adverse Events (SAEs) are defined as any untoward medical occurrence(s) that at any dose results in death, hospitalisation or prolongation of existing hospitalisation, persistent or significant disability/incapacity or a congenital anomaly or birth defect.

Suspected Serious Adverse reactions (SSARs) are any ARs considered consistent with information available about an Investigational medicinal Product (IMP).

As this study involves only a lifestyle modification, no SAEs or SSARs are expected.

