# ROLES AND RESPONSIBILITIES OF STUDY MANAGEMENT COMMITEES

INVESTIGATOR COMMITTEE

All investigators for the project will meet every 3 months to discuss progress of the study, strategy for delivery, risk management, review of safety and efficacy data, and dissemination of findings.

TRIAL COORDINATION COMMITTEE

The trial coordination committee will comprise of the Chief Investigator, Research Assistant and Trial Coordinator and will meet fortnightly to discuss day-to-day running of the project. Updates from these meetings will be provided for the investigator committee and PSC.

PROJECT STEERING COMMITTEE (PSC)

The PSC comprises of an independent Chair, an independent expert in the study area, a lay person, the principal investigator and one co-investigator and will meet every 6 months. The PSC will advise, via the Chair, on relevant aspects of the project to the funder, sponsor and host institution. It will monitor progress of the project, protocol adherence, substantial protocol amendments and participant safety. The PSC will also advise the investigators on all aspects of the project.

PATIENT AND PUBLIC ADVISORY GROUP (PPAG)

The PPAG will implement their terms of reference from the onset which will focus on three core areas; supporting the development and direction of the research, development of information resources and dissemination of research findings. The PPAG will be comprised of the immediate project group, an independent chair, a CCG diabetes lead for the local area, a diabetes nurse and two patients with Type 2 diabetes (T2D). The PPAG will meet every 3 months and have input as below:

MANAGEMENT OF THE RESEARCH: Advisory members will help to ensure the recruitment process is practical, feasible and effective. Members will provide ideas on recruitment methods, how to encourage people with T2D to volunteer, and how to raise the subject of sitting behaviour with the target population. Members will feedback on the protocols planned for delivery within the study and will help to solve issues that may arise during delivery of the study.

DEVELOPMENT OF INFORMATION RESOURCES: Advisory members will help to make language and content of information resources appropriate and accessible to potential volunteers, including questionnaires, information leaflets and consent forms. This will aid recruitment and help potential volunteers to make informed choices about their participation.

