# STUDY PROTOCOL

## BACKGROUND

There are more than 3 million people with Type 2 diabetes (T2D) in the UK, costing the NHS 10% of its annual budget (1). People with T2D have a high risk of cardiovascular disease (CVD), early death, poor psychological wellbeing and a burden of diabetes-related complications such as neuropathy, nephropathy and retinopathy that reduce quality of life (2-4). Improving glycaemic control is important for reducing the onset of these secondary outcomes (5, 6) and effective interventions thus need to be identified.

People with T2D spend 8.0-9.5 hours/day sitting (7-9). Sitting (sedentary behaviour) has been detrimentally associated with CVD (10); a leading cause of death in T2D (1). Each hour of sedentary time is detrimentally associated with CVD risk markers in people with T2D including waist circumference, insulin resistance and high-density lipoprotein cholesterol (HDL) (7). Importantly, the detrimental associations of sedentary time with T2D, CVD and psychological wellbeing are independent of time spent in moderate-to-vigorous physical activity (MVPA) (10, 11). At least 60-120 minutes/day of MVPA may be needed to protect against the increased mortality risk associated with high amounts of sitting (12, 13), which is an unrealistic target for most people. In T2D, each 1 minute increase in sedentary time is related with a 0.12 minute increase in time spent in hyperglycaemia (7.4 minute increase in hyperglycaemia for each extra hour of sitting) (14). Hyperglycaemia increases CVD risk (1) and is associated with poor psychological wellbeing (15). Each hour of sedentary time is also unfavourably associated with waist circumference, insulin and a clustered CVD risk score, while each break in sedentary time is associated with lower waist circumference and improved HDL (7, 8). Reducing total and prolonged sitting is thus an important target to reduce CVD risk and poor psychological wellbeing in people with T2D.

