### Participants

Participants will be aged 18-85 years with physician diagnosed or self-reported T2D who are able to ambulate unassisted and self-report sitting for ≥7 h/day (this is the threshold above which mortality risk increases) (44, 45). Exclusion criteria will be using insulin medication, unable to communicate in English, pregnant, and cognitive or physical conditions interfering with the ability to stand and ambulate (with or without the use of a walking aid). Diagnosis of T2D will be confirmed from the fasting glucose measure taken at baseline. Individuals with readings below the diabetes range (7 mmol/L) will at this stage be excluded from the study.

**COVID-19 contingency:** If it is not possible to take glucose measures at baseline due to COVID-19 restrictions, participants will not be required to fast overnight prior to data collection. Participants in this case will need to self-report Type 2 diabetes diagnosis. Each participant’s GP will be notified of their participation in the study; GPs will be asked to inform the research team if their patient does not have a Type 2 diabetes diagnosis.

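### The adverse event definition conflicts with the relatedness assessment and leaves non-serious control-arm events unclear, and the statement that no SAEs are expected does not fit the protocol's all-cause SAE definition

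*Protocol*

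**What the plan says.** All the rules on events are in the protocol's Safety Reporting section.

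- **AE definition:** "Adverse Events (AEs) are any unfavourable and unintended signs, including abnormal laboratory results, symptoms or a disease associated with treatment".
- **Recording:** each AE goes on a case report form, whose items include "severity, assessment of relatedness to study, and action taken".
- **Follow-up:** "AEs considered related to the study as judged by the Chief Investigator will be followed until resolution" or until the event is stable.
- **SAE definition:** "any untoward medical occurrence(s) that at any dose results in death, hospitalisation or prolongation of existing hospitalisation", with disability and congenital anomaly also listed. No link to treatment or arm is required.
- **Expectation:** the section closes with "As this study involves only a lifestyle modification, no SAEs or SSARs are expected".

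Elsewhere, the Participants section states "Participants will be aged 18-85 years with physician diagnosed or self-reported T2D", and the Background states "People with T2D have a high risk of cardiovascular disease (CVD), early death". Under Control group, the comparator is usual care with the same measurements as the intervention arm. Under Health coaching, intervention participants have an initial session and calls at about 2, 6 and 12 weeks. The section on committees says of the steering committee: "It will monitor progress of the project, protocol adherence, substantial protocol amendments and participant safety".

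**The concern.** There are two separate defects.

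First, if association with treatment is a condition for being an AE, the relatedness item on the form is redundant, because causality was settled before the event was logged. If relatedness is to be judged afterwards, the condition should not be in the definition. The condition also has no clear meaning for usual-care participants, who receive no study treatment. Two members of staff could reasonably log different things for the same control-arm event.

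Second, an SAE under this protocol is any death or hospitalisation from any cause. Saying that none are expected because the intervention is a lifestyle one gives a causal reason for a statement about an all-cause category. The section ends there and names nobody to whom an SAE is reported.

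At stake is whether the steering committee, which is charged with participant safety, receives event data that can be compared between the arms, and whether the study hands a later trial a working safety procedure.

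**Working it through.** **AE definition against the recording rule.** The definition can be read in two ways.

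1. The treatment condition applies to the whole list (signs, symptoms, disease). Then every AE is by definition associated with treatment. The relatedness item screens a second time for something already required, and a usual-care participant has no treatment for an event to be associated with.
2. The condition applies only to disease. Then signs and symptoms count in either arm, but a new non-serious illness in a control participant still does not clearly count.

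The recording and follow-up rules point to a third intention, which is to log everything, judge relatedness, and follow up only the related events. The definition does not say this. On each reading, some part of the section fails to fit or control-arm recording stays unclear. The uncertainty concerns non-serious events, because the SAE definition is neutral as to arm.

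**Opportunities to report.** Both arms attend data collection at baseline, 12 and 24 weeks. The intervention arm alone has four further scheduled contacts (one coaching session and three calls) and may contact coaches in between. No common AE question is stated for the shared contacts. If events surface through spontaneous mention, the intervention arm has more occasions to mention them.

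**How likely is at least one SAE?** The protocol gives no figure to reproduce.

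- Inputs: 70 participants (Sample size) and 24 weeks (Study design).
- Person-time: 70 x 24/52 = 32.3 person-years, or about 16.2 per arm, assuming complete follow-up.
- Expected SAEs: rate x 32.3. Chance of at least one: 1 - exp(-rate x 32.3).
- The rate is an assumption, so a range is shown.

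| Assumed rate per 100 person-years | Expected SAEs, both arms | Chance of at least one |
|---|---|---|
| 2 | 0.02 x 32.3 = 0.65 | 48% |
| 5 | 0.05 x 32.3 = 1.6 | 80% |
| 10 | 0.10 x 32.3 = 3.2 | 96% |
| 20 | 0.20 x 32.3 = 6.5 | 99.8% |

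A binomial calculation on 70 people gives the same probabilities. Solving backwards, an even chance of at least one SAE corresponds to ln(2)/32.3, about 2.1 per 100 person-years. A 95% chance of none would need -ln(0.95)/32.3, about 0.16 per 100 person-years. Loss to follow-up would lower these chances somewhat.

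**The case against.** The best defence is that the section is loosely worded but workable. Its relatedness item and its restriction of follow-up to related events make sense only if unrelated events are recorded too. The closing sentence opens with the nature of the intervention and pairs SAEs with suspected reactions, so it can naturally be read as speaking of harm caused by the intervention. On that reading it is defensible. The event rates are assumed: at 2 per 100 person-years the chance of no SAE is about 52%, and participants must walk unassisted and not use insulin. All of this stands. It limits the point to what the text secures and does not show that the wording is sound.

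A reader might infer more than the protocol supports:

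- **Events would come from one arm only.** No sentence restricts recording to the intervention arm, and the SAE definition covers both.
- **Hospitalisations are overlooked.** Hospitalisation is a named SAE criterion. What is missing is a stated recipient.
- **Musculoskeletal harm could not be told from background.** Musculoskeletal symptoms are measured by questionnaire in both arms at baseline, 12 and 24 weeks. Falls have no listed measure.
- **A full trial would inherit no usable safety rates.** With about 16 person-years per arm, a rate of 10 per 100 gives about 1.6 SAEs per arm. Even perfect capture could not give usable SAE rates, and such rates are not an objective.
- **There is no safety oversight.** The investigator committee reviews safety data every 3 months, and the steering committee monitors participant safety.

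The references to dose and to a medicinal product are leftover template wording with no shown effect on the data. Tabulation of events may be covered in an analysis plan that is not at hand.

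**Conclusion.** The concern holds as a defect in stated wording. The AE definition conflicts with the relatedness assessment and leaves the status of non-serious control-arm events unclear. With extra contacts in one arm and no common question, comparable capture is not secured; the protocol does not show that capture would actually differ.

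The statement on expected SAEs does not fit the protocol's own all-cause definition in this population unless it is limited to intervention-caused events. The chance of at least one SAE is 48% to 99.8% for assumed rates of 2 to 20 per 100 person-years, with complete follow-up of 70 people. The conclusion does not need the upper end, since a confident expectation of none (95%) would require a rate of about 0.16 per 100 person-years. The change should be made because it is cheap and concerns a rule that staff must apply from the first participant.

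**What to change.** Three changes to the Safety Reporting section:

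1. Define an AE as any untoward medical occurrence in any randomised participant, in either arm, whether or not it is thought related. Judge relatedness afterwards, on the existing form.
2. Ask both arms the same question about adverse events, falls and hospitalisations at the existing 12- and 24-week data collections.
3. Reword the closing sentence to say that no intervention-related SAEs are expected, and that all SAEs in both arms will be recorded and reported to the sponsor and the steering committee.

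The cost is a wording change, one extra question at contacts that already take place, and a few more events to log. No additional visit is needed, and the sample size and outcomes are unaffected.
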